#### Ancillary study—Participation of African-Americans in Cessation Trial (PACT)

To gain a better understanding of factors impacting trial refusal among Black individuals who smoke using a rigorous qualitative approach. This ancillary study was funded by an NCI Diversity Supplement.

### Conceptual framework

Two complementary evaluation frameworks, Proctor’s Implementation Outcomes Framework [25] and the Consolidated Framework for Implementation Research (CFIR), guide our assessment plan and selection of implementation outcomes [26]. Proctor’s Framework measures include (1) the intervention’s reach into the target population, (2) adoption (uptake of the intervention), (3) implementation fidelity, (4) acceptability (perception that treatment is satisfactory), (5) appropriateness (intervention fit/workflow compatibility), (6) sustainability (potential for sustained use/integration and barriers to achieving durability), and (7) cost [25]. We will also assess the organizational characteristics or “inner settings” constructs defined by the Consolidated Framework for Implementation Research (e.g., organizational priority, implementation climate, resources, leadership) that may influence the implementation of smoking cessation treatment in lung cancer settings [26].

### Study setting and site recruitment

This trial is being conducted at 17 LDCT-LCS sites across the USA. Recruitment of participating sites and site coordinators (SC) was led by the staff from the GO2 Foundation for Lung Cancer (GO2) (formerly Lung Cancer Alliance). Sites were eligible for participation in the CASTL trial if they were part of GO2’s Screening Centers of Excellence (SCOE) national network indicating having met several criteria for high-quality screening practices. Study sites were required to have at least 1 year of lung cancer screening experience, employ at least one SC, and report conducting at least 20 LDCT screenings per month so as to have an adequate patient volume for achieving the target recruitment of patients who smoke during the allotted study time frame. To promote participant diversity, there was attention paid to selecting a wide variety of LDCT-LCS sites both with and without academic affiliations and with geographic diversity across the USA. LDCT-LCS sites were recruited and onboarded in staggered waves.

### Patient eligibility

Consistent with the 2013 USPSTF recommendations for LDCT-LCS, eligible patient participants are between [27] the ages of 55–80 years old (at the time of their LDCT scan), seeking baseline or annual follow-up LDCT-LCS, have at least a 30-pack-year history of smoking, currently smoking (defined as self-reported cigarette smoking on some days or every day) within the past 30 days, reachable by telephone, and English speaking. In April 2021, the eligibility criteria were expanded to include patients who were between the ages of 50–80 years old (at the time of their scan), with at least a 20-pack-year history of smoking. To facilitate the inclusion of non-English speaking participants, the study materials were later translated into Spanish and Spanish-English bilingual staff were hired. Patients are excluded from participation if either nicotine replacement therapy (NRT) is medically contraindicated (e.g., recent heart attack within the last 2 weeks) or they presented severe medical or psychiatric comorbidities that may prevent them from participating fully in the study (per the discretion of the screening SC or the study’s principal investigators). Finally, patients who are receiving concurrent tobacco treatment services or have used cessation medications (NRT, bupropion, varenicline) within the past month with the intent to quit smoking are excluded. Black people who smoke who actively or passively refused participation in CASTL are approached for participation in the ancillary refusal study.

### Participant recruitment

Each site has a target enrollment of 64 participants (total *n* = 1152). All participants who report current smoking are identified by the SCs (or designee) who introduce the CASTL study to all eligible patients during scheduling for their LDCT scan. SCs provide names and contact information of interested patients to the Memorial Sloan Kettering Cancer Center (MSK) study staff daily. SCs also maintain a detailed screening log of all people reporting current smoking with LDCT-LCS appointments and provide weekly de-identified updates regarding the number of people currently smoking who were ineligible for CASTL and the reasons for ineligibility. Information reported includes the number of refusers, their reasons for refusal, and limited demographic characteristics (age, gender, race, and ethnicity) of all people who currently smoke seeking LDCT-LCS. These screening logs provide the information needed to determine the reach rate, the proportion of eligible, participants who enroll in the CASTL trial.

An MSK Clinical Research Coordinator (CRC) emails potential participants a study introduction letter shortly after interested participants are referred by the SCs and makes up to 3 telephone attempts to confirm their eligibility. Trained CRCs have a non-written (verbal) informed consent discussion with participants so as to confirm eligibility prior to randomization. Participants will receive study information by mail following these consent discussions. Initially, consent was obtained prior to their lung cancer screening visit, or within seven business days of the completion of their LDCT scan. However, the COVID-19 pandemic issues resulted in LDCT-LCS sites reporting closures, scheduling delays, and disruptions requiring a protocol amendment to allow for enrollment of eligible patients anytime in LDCT clinical workflow between 60 business days prior to the LDCT appointment and 60 business days following the scan.

Eligible Black patients who actively or passively refuse CASTL participation (patients who do not give permission to be contacted by the MSK coordinating staff) are given a brochure containing descriptive information about the ancillary refuser study and encouraged to contact the MSK study team by email or telephone. In addition, Black patients who initially gave permission to be contacted but subsequently actively or passively refuse participation in the CASTL trial are provided with a verbal description of the PACT study either during the telephone contact or emailed a description of the PACT study once all CASTL recruitment attempts have been made in an effort to engage them in the ancillary study. PACT participants will be verbally consented by the research scholar leading this ancillary study.

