### Study aims

#### Aim 1

To identify which of four evidence-based tobacco treatment components contribute to superior cessation endpoints among people who currently smoke and are seeking lung cancer screening over and above enhanced standard care (i.e., minimum intervention needed for change). The four tobacco treatment components being tested are (1) motivational interviewing (MI) (yes vs. no), (2) nicotine replacement therapy (NRT) patch (yes vs. no), (3) NRT lozenge (yes vs. no), and (4) message framing (gain vs. loss). We hypothesize that all four treatment component enhancements will be statistically superior to enhanced standard care alone and that some synergistic treatment component effects will emerge. For the message framing condition, we expect that gain-framed messages will result in higher quit rates. The primary cessation outcome is biochemically verified 7-day point abstinence at 6 months following study enrollment. Secondary cessation outcomes are self-reported 7-day point prevalence abstinence at 3 months, continuous abstinence (between the date of randomization and date of completion of follow-up surveys) at 3 and 6 months, and self-reported 24-h quit attempt at 3 and 6 months.

#### Aim 2

To estimate the cost and incremental cost-effectiveness of evidence-based tobacco treatment components, delivered alone and in combination.

#### Aim 3

To conduct a robust, mixed methods evaluation of the implementation process and assess site characteristics and organizational factors that may influence the implementation of tobacco treatment in lung cancer screening settings.

#### Aim 4

To analyze whether lung cancer screening results (i.e., Lung-RADS®) moderate smoking abstinence outcomes. We hypothesize that participants found to have one or more screening abnormalities will be more likely to quit smoking and maintain smoking abstinence.

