*Aim 3. To conduct a robust, mixed methods evaluation of the implementation process and assess site characteristics and organizational factors that may influence the implementation of tobacco treatment in lung cancer screening settings.*

Descriptive statistics will be used to summarize key implementation outcomes (reach, adoption, fidelity, acceptability, appropriateness) collected from SC surveys [25]. Site characteristics will also be used in exploratory analyses on variation in cessation and implementation outcomes to examine the extent to which site characteristics are associated with intervention effectiveness, fidelity, and acceptability. To better understand the implementation challenges and sustainability, semi-structured interviews with SCs will be conducted following the completion of study participation. Interviews will be audio-recorded and transcribed. Led by an experienced qualitative methods specialist (QMS), a team of trained and supervised coders will analyze the transcripts using NVivo Pro version 12.0, a qualitative data analysis management software program [70]. Coders will utilize a thematic text analysis approach, which will occur in two phases [60, 71, 72]. In the first phase, the team will iteratively develop a codebook based on a priori domains and inductive concepts that emerge from the data, meeting regularly to reach a consensus on code name and definition. Then, all transcripts will be independently coded, and the QMS will complete a quality assurance check of the dataset. In the second phase, the team will group coded statements into analytic domains, and review these categories to identify and describe major and minor thematic areas. Themes will include sentiments that appear across most transcripts, as well as any significant divergences.

*Aim 4: To analyze whether lung cancer screening results (i.e., Lung-RADS) moderate smoking abstinence outcomes.*

We will use the Lung-RADS category score (1–4) as an ordinal measure of lung cancer screening findings and examine whether the proportion of participants achieving smoking abstinence differs by the degree of screening abnormalities (Lung-RADS score).

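### Enrolment up to 60 business days after the scan screens out some people who quit because of their result, so the pooled Aim 4 comparison by Lung-RADS is probably attenuated, by an amount the article does not allow one to compute

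*Protocol article*

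**What the plan says.** All references are to the Protocol article.

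- **Study aims, Aim 4** states a directional hypothesis: "participants found to have one or more screening abnormalities will be more likely to quit smoking and maintain smoking abstinence".
- **Participant recruitment** first describes a narrow window, in which "consent was obtained prior to their lung cancer screening visit, or within seven business days of the completion of their LDCT scan". The COVID-19 amendment widened it to any time "between 60 business days prior to the LDCT appointment and 60 business days following the scan". The consent discussion is held "so as to confirm eligibility prior to randomization". The same section has coordinators "introduce the CASTL study to all eligible patients during scheduling for their LDCT scan", so part of the sample enters before any result exists.
- **Patient eligibility** requires the person to be "currently smoking (defined as self-reported cigarette smoking on some days or every day) within the past 30 days", and excludes "patients who are receiving concurrent tobacco treatment services or have used cessation medications (NRT, bupropion, varenicline) within the past month" where the purpose was to quit.
- **Primary outcome** times abstinence at 6 months from randomisation, not from the scan or the result.
- **Data analysis, Aim 4 paragraph** will treat Lung-RADS 1 to 4 as ordinal and "examine whether the proportion of participants achieving smoking abstinence differs by the degree of screening abnormalities". It does not mention whether the result was known at enrolment.
- **Trial status and modifications** lists the wider window, says it lets coordinators search their schedules in both directions, and notes no consequence for Aim 4.

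**The concern.** Lung-RADS category is not randomised, so randomisation gives Aim 4 no protection against selection at entry. For a participant approached after the result, eligibility is judged when the result may already have changed smoking behaviour. Someone who responded to an abnormal scan by stopping promptly, or by starting cessation medication or a cessation service, may no longer qualify. Someone who did not respond still does. If the Aim 4 hypothesis is right, such responders are more common after abnormal scans, so the abnormal-scan group loses more of its quitters before anyone is counted.

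A weak Lung-RADS association could then partly reflect when people were enrolled, and the plan as written could not tell that apart from a genuinely weak effect of the result.

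**Working it through.** **1. The plan's own figures.** The article gives no sample size, power or effect size for Aim 4. Its one power figure is for an Aim 1 component main effect: 1152 × 0.8 / 2 = 460.8 per level, effect 0.20 SD, two-sided 5%. Then 0.20 × √(460.8/2) = 3.04, 3.04 − 1.96 = 1.08, and power is 85.9% against the stated 85%. That figure reproduces and is not touched by this point, because the selection happens before randomisation.

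**2. Window against look-back.** 60 business days = 12 weeks = 84 calendar days. The smoking criterion looks back 30 days. Suppose a person stops unaided on day d after the scan, stays abstinent, and is equally likely to be called on any of the 84 days (an assumption). Smoking status rules that person out for (84 − d − 30)/84 of the window:

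| Quit day d | Share of window ineligible |
|---|---|
| 0 | 54/84 = 64% |
| 7 | 47/84 = 56% |
| 14 | 40/84 = 48% |
| 28 | 26/84 = 31% |

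Under the original limit, 7 business days is 9 to 11 calendar days. That is shorter than 30, so the look-back ruled out nobody who quit unaided after the scan. This part of the problem comes from the amendment. The medication and concurrent-service exclusion takes effect at once and applied under both windows.

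**3. Illustration of the effect on Aim 4.** All rates here are assumed; none is in the article. Let 14% quit after enrolment whatever the result, and let result-prompted quitting be 3% after a negative and 12% after a positive scan.

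- Enrolled before the result: 1 − 0.86 × 0.97 = 16.6% and 1 − 0.86 × 0.88 = 24.3%. Difference 7.7 points, OR 1.62.
- Enrolled after the result, with a fraction q of prompted quitters already ineligible: abstinence = 1 − 0.86 × (1 − r)/(1 − q·r), with r = 0.03 or 0.12.
  - q = 0.56 (the day-7 figure above): 15.2% v 18.9%.
  - q = 1: 14% v 14%.
- Half the enrolees late, the two groups averaged:
  - q = 0.56: 15.9% v 21.6%, difference 5.7 points, OR 1.46.
  - q = 1: 15.3% v 19.2%, difference 3.9 points, OR 1.31.
- With q = 0.56 and 25% or 75% late, the difference is 6.7 or 4.7 points. The loss is thus about 13%, 26% and 39% at 25%, 50% and 75% late.

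**4. Sensitivity to the assumed rates.** Take the article's illustrative Aim 1 rates, 20% and 12%, as abstinence after positive and negative scans (8 points), with half late by intention. If only the extra 8 points can be lost, with e = 0.08q, the positive-scan rate is (0.5 × 0.20 + 0.5 × (0.20 − e)) / (0.5 + 0.5 × (1 − e)).

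- q = 0.56: 0.1776/0.9776 = 18.2%, difference 6.2 points.
- q = 1: 0.160/0.960 = 16.7%, difference 4.7 points.
- Harsher case, in which all 20% quit promptly and only the positive-scan group loses quitters (e = 0.20q): the difference is 3.3 points at q = 0.56 and −0.9 at q = 1.

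**The case against.** The strongest reply has four parts.

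*The exclusion is partial.* This stands. A reader might infer that anyone who quits because of the result cannot enter. The documents do not support that. Some-day smoking within the past 30 days qualifies, so an unaided quitter remains eligible for up to 30 days, and a person who cut down, or who tried unaided and relapsed, can enter. Everyone enrolled before the result is unaffected, and the study is introduced at scan scheduling. Late enrolees are therefore not simply people whom the result failed to move, and Aim 4 also concerns maintaining abstinence, which can still be affected after enrolment.

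*The size is unknown.* This also stands. The article does not give the share enrolled after the result, and recruitment began in August 2018, before the COVID-19 amendment. A reader might conclude that a quarter to three quarters of the effect is lost. That follows only if the effect among late enrolees is set to zero, in which case the loss simply equals whatever late share was assumed.

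*The spread in follow-up is not in itself a bias.* The scan-to-outcome interval can run from about 26 − 12 = 14 weeks to 26 + 12 = 38 weeks. This distorts the Lung-RADS comparison only if enrolment timing differs by Lung-RADS, which nothing in the article shows.

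*A condensed article may leave the modelling elsewhere.* This stands only in part. Covariates and interaction terms may well be in the full protocol or an analysis plan. But the article itself fixes the window, the entry criteria and the Aim 4 contrast, and following that contrast as stated gives an estimate from a selectively depleted group.

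**Conclusion.** The point holds as a limited one. After the amendment, some people who quit in response to their result are screened out before randomisation. If the Aim 4 hypothesis is true, the loss is greater among abnormal scans and the pooled Lung-RADS association is probably attenuated. Under the assumed rates, with half enrolled late, 7.7 points becomes about 5.7 if 56% of prompted quitters are ineligible and 3.9 if all are. The true amount cannot be computed from the article.

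Attenuation is the expected direction, not an established one: with strong depletion confined to positive scans the association could reverse. A reader might go further and infer that a null Aim 4 result would be an artefact; that is not supported, because neither the late share nor the amount of depletion is known. Nor does the point reach Aim 1, whose randomised comparisons keep their internal validity.

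**What to change.** In the Aim 4 paragraph of Data analysis:

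- Present the Lung-RADS association separately for participants randomised before and after they received their result. Equivalently, include an indicator for result known at randomisation and its interaction with Lung-RADS.
- Name the pre-result group as the estimate that addresses the hypothesis.
- State that the post-result group under-represents quitting prompted by the result, and report how many participants fall in each group.
- Adjustment for time from scan to outcome is optional.

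This changes analysis wording only. Scan and randomisation dates are needed to apply the enrolment window, and the framed message is already timed from receipt of results. According to Trial status and modifications, analysis is to begin only after data collection ends. The cost is lower precision for Aim 4, since fewer participants inform its main estimate.

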### Patient randomization and assignment to treatment group

Eligible patients who smoke are registered via MSK’s Clinical Trials Management System to the CASTL trial and randomized using the Clinical Research Database by a CRC. Individual study participants are randomized to one of the 16 intervention combinations listed in Table 1. Randomization is stratified using the method of the random permuted block by participating LDCT-LCS site. After patient registration and randomization, a designated MSK CRC sends each SC a secure email containing the patient’s treatment assignment.

**Table 1 Tab1:** Treatment components

Components					
Conditions	Enhanced standard care	Motivational interviewing	NRT lozenge	NRT patch	Message framing
**1**	Yes	Yes	No	No	Loss
**2**	Yes	Yes	No	No	Gain
**3**	Yes	Yes	No	Yes	Loss
**4**	Yes	Yes	No	Yes	Gain
**5**	Yes	Yes	Yes	No	Loss
**6**	Yes	Yes	Yes	No	Gain
**7**	Yes	Yes	Yes	Yes	Loss
**8**	Yes	Yes	Yes	Yes	Gain
**9**	Yes	No	No	No	Loss
**10**	Yes	No	No	No	Gain
**11**	Yes	No	No	Yes	Loss
**12**	Yes	No	No	Yes	Gain
**13**	Yes	No	Yes	No	Loss
**14**	Yes	No	Yes	No	Gain
**15**	Yes	No	Yes	Yes	Loss
**16**	Yes	No	Yes	Yes	Gain

#### Tobacco treatment components

Careful attention was given to the selection of tobacco treatment components guided by the following principles: (a) evidence-based, (b) feasible and scalable for high and low resource LDCT-LCS sites, and (c) sustainable beyond the CASTL study period. The study is designed to compare enhanced standard care (control group) with four tobacco treatment components: (1) motivational interviewing (MI) (yes vs. no), (2) nicotine replacement therapy (NRT) patch (yes vs. no), (3) NRT lozenge (yes vs. no), and (4) message framing (gain vs. loss).

##### Enhanced standard care

SCs provide all CASTL participants with self-help, print cessation materials targeting persons who currently smoke seeking lung cancer screening, *Why Quit Now? A Resource for Those at Risk for Lung Cancer* [28] and refer patients to the national Quitline at [name] for education and follow-up cessation counseling during their first session within 1 month of randomization or during the shared decision-making discussion. Enhanced standard care was chosen as the comparator to ensure that at minimum, all participants receive cessation advice and an active referral to the Quitline, a service that was not consistently provided to participants prior to CASTL.

##### Motivational interviewing (MI) [29]

There is substantial evidence that even brief MI can increase adherence to tobacco treatment and quit rates [30]. Participants assigned to the MI component receive two MI counseling sessions delivered by the SC; the first delivered face to face or via telephone during the patient’s lung cancer screening visit, and the second session, delivered via telephone by the SC approximately 1 to 8 weeks after participants receive their LDCT scan results. In response to the difficulties reaching patients during the COVID-19 pandemic, we amended the protocol to allow SCs to deliver the first session of MI (including the enhanced standard care) within 1 month of the participant’s randomization to the study.

##### Nicotine lozenge [31, 32]

Participants randomized to this treatment component receive 6 cartons of 2 mg lozenges (81 units/carton) by mail, along with written instructions to use the lozenges to help manage acute nicotine withdrawal. Participants are instructed to use the NRT lozenges no more than every 1–2 h as needed and up to 20 lozenges per day during their initial session with the site coordinator for a period of 6 weeks.

##### Nicotine patch

Participants randomized to receive this treatment component receive 6 weeks of nicotine patch with dosing dependent upon baseline cigarettes per day, along with written instructions for safe and effective use by mail [31]. Participants who smoke fewer than 10 cigarettes per day receive 4 weeks of the 14 mg patch (2 boxes) and 2 weeks of the 7-mg patch (1 box). Those who smoke 10 or more cigarettes per day receive 2 weeks of the 21-mg patch (1 box), 2 weeks of the 14-mg patch (1 box), and 2 weeks of the 7-mg patch (1 box) and are instruction about proper usage during their initial session.

